#### Recruitment

In both studies, patients will be recruited at regular bi-annual visits for diabetes control. Nurses specializing in diabetes will send detailed information about the study together with calls for diabetes controls to patients without known criteria for exclusion. At the diabetes control visit, the information will be repeated, and re-evaluation for prevalent exclusion criteria will be performed. The recruitment period will last for 9 months at each unit. Baseline data and measurements (T0) will be collected after signed informed consent has been obtained. The patients are informed that they can withdraw from the study at any time without negative consequences.

#### Randomization and allocation

The randomization and allocation of the coded patients will be performed by an independent statistician with the purpose of having as equal distribution as possible of sex and age in each intervention arm.

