#### Study II

This is a multicentre open-labeled parallel-group study with a three-arm randomized controlled trial design, which will start in 2016 and will be completed in 2023 for patients with type 2 diabetes recruited from primary care units.

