### Treatment as usual

In both studies, there will be no restriction on the use of treatment as usual, such as psychotherapeutic or physiotherapeutic treatment, antidepressant medication or diabetes-related treatment.

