#### Study II

The power calculation is based on an analysis of variance (ANOVA), where two groups have the same means and one differs with 1.4 points, using the same standard deviation (2.8) as in Study I. Calculating a statistical power of 80 %, calculated using an ANOVA, 60 persons are required. However, using the Kruskal–Wallis test reveals that it is necessary to increase this by 15 %; thus, 70 persons are required in each arm in a three-arm randomized controlled trial.

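### Multicentre Study II names only sex and age as balancing factors, and its planned rank test has no unit term: a small, avoidable loss of precision

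*Protocol article*

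**What the plan says.** The rule under Randomization and allocation precedes the separate Study I and Study II paragraphs and so covers both. Its stated aim is allocation "with the purpose of having as equal distribution as possible of sex and age in each intervention arm". The Study II paragraph that follows lists the three arms and the non-randomised groups and adds no balancing factor.

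Under Study design, Study II is described thus: "This is a multicentre open-labeled parallel-group study with a three-arm randomized controlled trial design". It takes "patients with type 2 diabetes recruited from primary care units". Under Recruitment, "The recruitment period will last for 9 months at each unit". Under Treatment as usual, for both studies, "there will be no restriction on the use of treatment as usual".

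Under Statistical analysis, changes in psychological symptoms in Study II are compared by the Kruskal-Wallis test. HbA1c gets a paired t test, and linear regression relates outcomes to baseline characteristics. Unit is not named in any of these.

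**The concern.** A rule that is adequate for one hospital clinic is carried unchanged into a trial with several recruiting units. If outcomes vary between units, an allocation that ignores unit lets units fall unevenly over the three arms. An analysis without unit then leaves that variation in the error term. The article does attend to clustering by instructor and by therapy group, but not by recruiting unit.

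What is at stake is precision. Study I reached about 21 per arm against 64 required, and the Discussion foresees recruitment difficulties. A gain that needs no additional patients is therefore worth having. The allocation part can only be changed before patients are randomised.

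**Working it through.** **1. The plan's own figure.** Inputs from Power calculations, Study II: three arms "where two groups have the same means and one differs with 1.4 points", "using the same standard deviation (2.8) as in Study I"; then "Calculating a statistical power of 80 %, calculated using an ANOVA, 60 persons are required", read as per arm. Significance level 0.05.

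- Means 0, 0, 1.4 have grand mean 0.467. The sum of squared deviations is 2 × 0.467² + 0.933² = 1.307.
- Noncentrality λ = n × 1.307 / 2.8² = n / 6.
- Noncentral F with 2 and 3n − 3 degrees of freedom: n = 59 gives 80.1 %, n = 60 gives 80.8 %.
- With the 15 % increase for Kruskal-Wallis, 60 × 1.15 = 69, against the stated 70.

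The plan's figure is reproduced. At n = 70, λ = 11.67 and ANOVA power is 86.9 %. This is the yardstick below. The plan's 15 % allowance brings the rank test back to roughly 80 % (70 / 1.15 = 60.9).

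**2. How uneven can units be?** Assume allocation ignores unit and totals are 70/70/70. Unit sizes are also assumed.

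| Unit size | Mean gap, largest to smallest arm | Chance that one arm has at least twice another |
|---|---|---|
| 10 | 3.0 | 78 % |
| 20 | 4.2 | 45 % |
| 40 | 5.6 | 15 % |

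Uneven spread within a unit is likely under this assumption, but these figures do not measure the effect on the trial's comparison.

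**3. Effect on the comparison.** Let ICC be the share of outcome variance explained by unit (assumed 0.01 to 0.10). The unit part of a two-arm difference has SD 2.8 × √(2 × ICC / 70). The total standard error is 2.8 × √(2 / 70) = 0.47, and the target difference is 1.4.

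- ICC 0.01: 0.05 points
- ICC 0.02: 0.07 points
- ICC 0.05: 0.11 points
- ICC 0.10: 0.15 points

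In simulations with 5, 10 or 20 equal units and ICC 0.02 to 0.10, the Kruskal-Wallis type I error under allocation ignoring unit was 4.6-5.3 %. The test stays valid.

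**4. Gain from balancing and adjusting.** Removing the unit variance gives λ = n / [6 × (1 − ICC)], with error degrees of freedom reduced by the number of units minus one.

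| ICC | λ at n = 70 | Power at n = 70 | n per arm for 80 % |
|---|---|---|---|
| 0 (no unit effect, no unit term) | 11.67 | 86.9 % | 59 |
| 0.01 | 11.78 | 87.2 % | 59 |
| 0.02 | 11.90 | 87.5 % | 58 |
| 0.05 | 12.28 | 88.6 % | 56-57 |
| 0.10 | 12.96 | 90.3 % | 54 |

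The number of units (5, 10 or 20) barely changes these results.

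**5. Limits on how to do it.**
- Balancing on unit while keeping the plain Kruskal-Wallis test makes it mildly conservative: simulated type I error 4.5-4.9 % at ICC 0.02, 4.2 % at 0.05 and 3.8-4.2 % at 0.10.
- Ranking strictly within units can lose power: 83 % against 85 % in a simulation at ICC 0.02.
- Fully crossing sex, two age bands (assumed) and 5, 10 or 20 units gives 20, 40 or 80 strata. With 3 × 70 = 210 patients, that is 10.5, 5.3 or 2.6 per stratum.

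**The case against.** The strongest reply is that a condensed article states an aim, not a method. It does not say that sex and age are the only factors, and it does not name simple, blocked or minimised allocation. If each unit's patients were allocated as one batch into equal arms, units would be nearly balanced anyway. The table of uneven spread is therefore conditional, and that part of the reply stands.

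A reader might also infer that usual care differs between units and so confounds the arms. The article says only that usual care is unrestricted. It does not say that units differ, and individual randomisation means that chance imbalance is not bias. Several features argue for a low ICC: one region, one laboratory department for HbA1c, a small shared set of instructors, and a primary outcome defined as change, which removes stable level differences between units. That stands too, and it points to the lower rows of the gain.

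What does not stand is that this is merely detail left for another document. The article does name its balancing factors, in a rule shared with a single-clinic study, and names none specific to the multicentre one. Adjustment can be added to a later analysis plan; balance cannot be added after randomisation.

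**Conclusion.** The point holds as a minor design improvement. Study II names only sex and age for balance, and its planned rank test has no unit term. The cost is a little precision: ANOVA power at 70 per arm of about 87 % instead of 88-90 % at an ICC of 0.02 to 0.10, and almost no difference at 0.01. The ICC, number of units and equal unit sizes are assumptions. The required 70 per arm is not affected.

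Three stronger readings are not supported. The comparison is not biased, since the simulated type I error stays near 5 %. The change is not free: it needs no patients, but it does need grouping of small units and a change in the analysis. And the recruitment sentence fixes a period at each unit; it does not say that units recruit one after another.

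**What to change.** Before Study II starts, have the independent statistician add primary care unit to sex and age in a minimisation-type allocation with a random element, not fully crossed strata. In the analysis, fit a model for change in HADS depression and in HbA1c with arm and a random intercept for unit.

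The cost is one more allocation variable and one more analysis. Very small units must be grouped beforehand, and the therapy groups of five to seven must still be filled. The plan should state whether the model replaces the Kruskal-Wallis test or stands beside it, and which of the two is primary. Ranking strictly within small units should be avoided, because it can lose power when the ICC is small.

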##### Study I

This is outlined in Fig. 2. Patients who fulfilled the criteria were randomized into two intervention arms, ASSA (group 1) or BBAT (group 2). After allocation, the ASSA and BBAT instructors offered renewed oral information and patients made their final decisions regarding participation. Group 3 consists of patients who fulfilled the criteria but refused participation after allocation, and group 4 consists of patients who did not fulfil the criteria. Groups 3 and 4 will be followed as comparison groups.

**Fig. 2 Fig2:**
[figure not shown]
Study flow chart for Study I

##### Study II

This is outlined in Fig. 3. Patients fulfilling the intervention criteria will be randomized into three arms: ASSA (group 1), BBAT (group 2) or no intervention (treatment as usual; group 3). Group 4 will consist of patients who fulfil the criteria but refuse participation after allocation. Group 5 will consist of patients who do not fulfil the criteria.

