#### Schedule for assessments

##### Study I

This is shown in Fig. 2. Assessments were performed for participants in ASSA and BBAT at baseline (T0), prior to intervention (T1) and after termination of the intervention (T2) and will be performed 7 years after T0 (T4). For nonparticipants (Groups 3 and 4), assessments were performed at T0 and will be repeated at T4.

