##### Study II

Assessments will be performed for Groups 1, 2 and 3 at T0, T1 and T2; 1 year after T2 (T3) and at T4. For Groups 4 and 5, assessments will be performed at T0 and T4.

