### Intention to treat analysis

#### Studies I and II

Differences at T0 between participants and nonparticipants fulfilling criteria will be analyzed regarding age, sex, self-reported depression and anxiety, alexithymia, self-image, clinical psychiatric diagnoses, smoking, physical inactivity, metabolic variables, medication and sick-leave status and will be thoroughly described. Levels of HbA1c will be determined for all patients who participate in the interventions, but decline to complete the questionnaires at T2, T3 (Study II only) or T4. At T4, all patients who participated at T0 will be asked for oral and written consent to participate in all the assessments, measurements and data collection that are included at T4. If full assessments are not possible we will collect data regarding HbA1c concentrations, mortality, diabetes complications and use of antidepressants.

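### Patients who refuse after allocation leave their randomised arm, so the T2 and T3 comparisons include acceptors only, and the plan does not commit to analysing refusers as randomised at T4

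*Protocol article*

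**What the plan says.** Under Randomization and allocation, Study I gives the order of events: "After allocation, the ASSA and BBAT instructors offered renewed oral information and patients made their final decisions regarding participation". Those who declined form a new group: "Group 3 consists of patients who fulfilled the criteria but refused participation after allocation". Of that group and of the patients who did not meet the criteria, the article says "Groups 3 and 4 will be followed as comparison groups". For Study II the rule is the same: "Group 4 will consist of patients who fulfil the criteria but refuse participation after allocation". The consent section places an oral consent after allocation in both studies.

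The Schedule for assessments limits what is collected from refusers. In Study I, "For nonparticipants (Groups 3 and 4), assessments were performed at T0 and will be repeated at T4". In Study II, "For Groups 4 and 5, assessments will be performed at T0 and T4". Participants are also assessed at T1 and T2, and in Study II at T3.

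The section headed Intention to treat analysis describes baseline differences between participants and nonparticipants. It then says "Levels of HbA1c will be determined for all patients who participate in the interventions, but decline to complete the questionnaires at T2" (or at the later visits), which covers only people who took up an intervention. For the last visit it is wider: "At T4, all patients who participated at T0 will be asked for oral and written consent to participate in all the assessments". If the full assessment is not possible, HbA1c, mortality, complications and antidepressant use are collected. The section does not say that patients are analysed in the arm to which they were randomised.

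**The concern.** Randomisation protects a comparison only if the groups compared are the groups that were randomised. Here membership of the compared groups is settled after the arm is known, by a decision that may depend on the arm. Refusers from different arms are then merged into one group, which in Study I is named a comparison group.

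The article gives reasons to think refusal could differ by arm. The Discussion says BBAT may be more easily accepted, because talking about emotions in a group can be stressful. In Study II the usual-care arm has no therapy to decline. If refusal differs, or if different kinds of patient refuse in different arms, part of the observed difference in depression change at T2 or T3 reflects who agreed to take part. The contrast with usual care, which is Study II's stated aim, is the most exposed. Refusal may also be common: the Discussion reports that too few Study I patients agreed to the intervention and foresees recruitment difficulties.

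A later analysis plan cannot repair T2 and T3, because it cannot recover depression scores that were never collected.

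**Working it through.** **The plan's own figures.** The Power calculations section uses an SD of change of 2.8 and a target of 1.4 points (0.5 SD), with 80 % power and a 0.05 level (taken as two-sided).
- Study I: the two-sample t test gives 63.8, so 64 per arm, as stated. Power with 21 per arm is 36.7 % (normal approximation) or 35.3 % (t test), against 37 % stated.
- Study II: ANOVA with means 0, 0, 1.4 has f = 0.236 and gives 58.8, so 59 per arm, against 60 stated. Then 60 × 1.15 = 69, against 70 stated.

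These reproduce closely. The problem is not arithmetic; it is which patients are compared.

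**What is available for refusers, by visit.**
- T1 and T2, both studies: no assessment.
- T3: does not exist in Study I; no assessment in Study II.
- T4, both studies: full assessment is requested, including the self-report instruments. The fallback data contain no depression score.

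An as-randomised comparison of depression change is therefore impossible at T2 and T3 under the schedule. At T4 it is feasible but not promised.

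**Size of the distortion.** Let r be the refusal rate in an arm, A the acceptors' mean change and A + d the refusers' mean change.
- As-randomised mean of the arm: (1 − r)A + r(A + d) = A + rd.
- An acceptors-only mean therefore misses rd.
- If d is the same in both arms, the contrast between arms 1 and 2 is shifted by (r1 − r2) × d in absolute size.

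The documents give neither r nor d. Assumed: r1 − r2 = 0.20, and d = 0.7 to 1.4 points.
- 0.20 × 0.7 = 0.14 points; 0.14 / 1.4 = 10 % of the target.
- 0.20 × 1.4 = 0.28 points; 0.28 / 1.4 = 20 % of the target.

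If d differs between arms, the shift is r1·d1 − r2·d2, which need not be zero even when refusal rates are equal.

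**Numbers.** The 10 % allowance is for unanswered questionnaires only. For Study II, 70 / 0.9 = 77.8, so 78 per arm.
- If 78 counts patients after refusal, 78 × 0.9 = 70.2 and the plan holds.
- If 78 counts patients before refusal, an assumed 20 % refusal leaves 78 × 0.8 × 0.9 = 56.2 responding acceptors.

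The article does not say which count is meant.

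**Effect of keeping refusers in their arm.** If refusers gain nothing, the expected effect is 1.4 × (1 − r). With 64 per arm and a two-arm t test:

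| Assumed refusal | Effect (points) | Power at 64 per arm | n per arm for 80 % |
|---|---|---|---|
| 10 % | 1.26 | 71 % | 79 |
| 20 % | 1.12 | 61 % | 100 |
| 30 % | 0.98 | 50 % | 130 |

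This is why it also matters to reduce refusal after allocation.

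**The case against.** A reader might infer that neither study can deliver any intention-to-treat comparison. The documents do not support that. Everyone seen at T0 is to be asked for the full T4 assessment, an independent statistician performs the allocation, and the abstract ties the sample sizes to the last follow-up session. The outcomes section names no time point, so T4 may be the visit that matters most. HbA1c, mortality, complications and antidepressant use are also to be collected at T4 when the full assessment is not possible. This objection stands, and it confines the point to T2 and T3 and to the missing commitment at T4. The T4 route still has limits: it needs new consent, its fallback omits depression, and in Study I it falls 7 years after T0.

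A reader might also infer that usual care keeps every patient. That too goes beyond the text. Group 4 is not restricted to the active arms, usual-care patients still face repeated assessments, and anyone may withdraw. Lower refusal there is plausible; zero refusal is an assumption. For ASSA against BBAT the gap in refusal could be small.

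Nor do the documents show that Study II will fall below 70 per arm. The Study I figure of around 21 per arm may itself count acceptors, in which case refusal does not reduce the planned number.

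Finally, analysis-set definitions are often left to a fuller plan, and the flow charts are not shown. That does not answer the point, because the regrouping and the assessment schedule are stated in the text.

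**Conclusion.** The point holds in this form. As written, both studies move patients who refuse after learning their allocation into a pooled group assessed only at T0 and T4. Comparisons at T2, and at T3 in Study II, are therefore between self-selected acceptors. The Intention to treat analysis section does not repair this, and it does not commit to using the planned T4 data by allocated arm.

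The size is unknown because no refusal rate is given. The shift of 0.14 to 0.28 points rests on an assumed 20-point gap in refusal, an assumed refuser–acceptor difference of 0.7 to 1.4 points, and that difference being equal across arms. With no gap in refusal and an equal difference, the shift is zero. Because the primary outcome is affected and, under Trial status, Study II had yet to start recruiting, the change should be made before that study begins.

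**What to change.** **Study II.**
- Give the renewed oral information on all three arms, and take the decision on participation, before randomisation.
- Keep every randomised patient in the allocated arm for the primary analysis, whatever they attend.
- Ask those who refuse or stop, with their agreement, to complete the HADS and TAS-20 at T2 and T3, and take their HbA1c from medical records and the diabetes register.
- State whether the inflated sample size counts patients before or after refusal.

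**Study I.** Analyse T4 with Group 3 returned to the allocated arms, and label the T2 analysis as acceptors only.

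**Both studies.** Describe any comparison with the refuser group as non-randomised. Rewrite the Intention to treat analysis section so that it defines the analysis set by allocated arm and says at which visits this applies.

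**Cost.** Some extra mailed questionnaires, a changed consent step (oral consent is now taken after allocation), and a possibly smaller effect estimate once patients who do not attend are included. In Study I only the analysis and its labelling can still change.

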**Fig. 3 Fig3:**
[figure not shown]
Study flow chart for Study II

#### Schedule for assessments

##### Study I

This is shown in Fig. 2. Assessments were performed for participants in ASSA and BBAT at baseline (T0), prior to intervention (T1) and after termination of the intervention (T2) and will be performed 7 years after T0 (T4). For nonparticipants (Groups 3 and 4), assessments were performed at T0 and will be repeated at T4.

##### Study II

Assessments will be performed for Groups 1, 2 and 3 at T0, T1 and T2; 1 year after T2 (T3) and at T4. For Groups 4 and 5, assessments will be performed at T0 and T4.

#### Assessments, measurements and data collection at T0 and T4

##### Studies I and II

Assessments will be performed using self-report instruments; HbA1c concentration, midnight salivary cortisol concentration, blood lipids, blood pressure, and anthropometrics will be measured (Figs. 2 and 3). Data will be retrieved from computerized medical records and from the Swedish national diabetes register. At T4, mortality data will be collected from the Swedish causes of death register.

#### Assessments and measurements at T1, T2 and T3

For Study I, assessments will be made using self-report instruments and HbA1c concentrations will be measured at T1 and T2 (Fig. 2).

For Study II, assessments will be performed with self-report instruments and HbA1c will be measured at T1, T2 and T3 (Fig. 3).

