### Power calculations for sample size

The standard deviation was 2.8 for the individual changes of Hospital Anxiety and Depression Scale – depression subscale after our intervention with ASSA for patients with chronic benign pain (calculated from raw data) [32].

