#### Study I

If we assume that the standard deviation for the individual changes in Hospital Anxiety and Depression Scale – depression subscale in this study is 2.8, a change of 1.4 points represents half the standard deviation, which is considered indicative of clinically relevant changes in subjective symptoms [52]. Calculating a statistical power of 80 %, and assuming significance at the 0.05 level, 64 persons in each intervention arm are required at follow-up in a two-arm randomized controlled trial. Unfortunately we only recruited around 21 persons in each arm in Study I, rendering a power of 37 %.

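### Study I leaves HbA1c unobserved for about 6 to 6.8 years after T2, and the only test named for it does not compare the arms; routine values and a between-arm longitudinal model would be a cheap, minor improvement

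*Protocol article*

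**What the plan says.** All references are to the Protocol article.

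- **Schedule.** HbA1c is measured at T0 and T4 in both studies (Assessments, measurements and data collection at T0 and T4). For Study I, "HbA1c concentrations will be measured at T1 and T2" (Assessments and measurements at T1, T2 and T3). Study II adds T3, one year after T2. In Study I, T4 is 7 years after T0 (Schedule for assessments).
- **Between visits.** Only medication changes are listed for collection between measuring points.
- **Routine contact and sources.** Under Recruitment, "patients will be recruited at regular bi-annual visits for diabetes control". For T0 and T4, "Data will be retrieved from computerized medical records and from the Swedish national diabetes register". The list of record and register variables under Data collection does not name HbA1c.
- **Incomplete T4.** Under Intention to treat analysis: "If full assessments are not possible we will collect data regarding HbA1c concentrations, mortality, diabetes complications and use of antidepressants". The source of those HbA1c values is not named.
- **Analysis.** Statistical analysis gives a paired-samples t test for HbA1c, plus linear regression relating outcomes to baseline characteristics. Treatment arm is not named as a term in that regression.

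**The concern.** The Background links high HbA1c to diabetes complications, and complications and mortality are outcomes, so the course of glycaemic control over years matters. With nothing scheduled between T2 and T4 in Study I, a benefit that lasts two years and then fades looks the same as one lost within months of T2. Glucose-lowering medication is tracked throughout this period, but HbA1c is not.

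A paired t test asks whether HbA1c changed within a group. It does not estimate the difference between ASSA and BBAT, which is the stated aim of Study I. With about 21 patients per arm, further information per patient is one of the few gains still open, and a record query can be made retrospectively.

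**Working it through.** **1. The plan's own figures.** Inputs from Power calculations for sample size: "The standard deviation was 2.8 for the individual changes"; "a change of 1.4 points represents half the standard deviation"; "assuming significance at the 0.05 level" (two-sided assumed); 80 % power. Normal approximation: n = 2 × (1.96 + 0.84)² / 0.5² = 63 per arm; the noncentral t gives the stated 64. At 21 per arm: 0.5 / √(2/21) = 1.62, and Φ(1.62 − 1.96) = 36.7 %, the stated 37 %. These figures concern the depression score and are unaffected. The article gives no power figure, SD or correlation for HbA1c.

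**2. Length of the gap in Study I.** Gap = 7 years − (T0 to T1) − intervention. ASSA takes 8 + 10 = 18 weekly sessions. BBAT has 10 weekly group sessions, and the interval of its five individual sessions is not stated. T0 to T1 is not stated either; 0 to 9 months is assumed, guided by the 9-month recruitment period.
- ASSA: 7 − 0 − 18/52.18 = 6.7 years; 7 − 0.75 − 18/52.18 = 5.9 years.
- BBAT, 10 to 15 weeks: 6.0 to 6.8 years.

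**3. Precision model (assumed).** HbA1c has unit variance, and the mean of k post-values is adjusted for the two pre-intervention values T0 and T1. With constant correlation ρ:

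V(k) = (1 + (k − 1)ρ)/k − 2ρ²/(1 + ρ)

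Under decay, the correlation between values at times s and t (years) is ρ₀ × φ^|s − t|, and V is the corresponding conditional variance of the mean. Assumed times: T0 = 0, T1 = 0.25, T2 = 0.6, T4 = 7. Power = Φ(d/√(2V/n) − 1.96), with an illustrative d = 0.35 SD and n = 21.

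**4. First year after therapy: T2 alone against T2 plus two routine values** (at 1.1 and 1.6 years).
- Constant ρ = 0.7: V(1) = 1 − 0.576 = 0.424; V(3) = 0.800 − 0.576 = 0.224; ratio 0.53. Power 41 % to 67 %.
- ρ₀ = 0.7, φ = 0.8: V = 0.521 and 0.349; ratio 0.67. Power 35 % to 48 %.
- Over ρ₀ = 0.6 to 0.85 and φ = 0.8 to 1.0, the variance ratio is 0.52 to 0.85.
- Study II, where T2 and T3 already cover this year: the ratio against T2 + T3 is 0.81 to 0.95.

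**5. Whole follow-up: mean of T2 and T4 against 14 post-values at 6-month spacing.**
- Constant ρ = 0.7: V(2) = 0.850 − 0.576 = 0.274; V(14) = 0.721 − 0.576 = 0.145; SE ratio √(0.145/0.274) = 0.73. Over ρ = 0.4 to 0.8 it is 0.67 to 0.74, a cut of 26 to 33 %.
- Decay, ρ₀ = 0.70 to 0.85 and φ = 0.8 to 0.9: SE ratio 0.89 to 1.02, a cut of 11 % down to none. A lower ρ₀ of 0.6 gives 0.83 to 0.84.
- If bi-annual means every two years (4 post-values): 0.83 to 0.86 at constant correlation and 0.93 to 0.99 under decay with ρ₀ = 0.70 to 0.85.

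**The case against.** The strongest reply is that measuring at fixed visits is a legitimate design for a secondary outcome, that nothing here is contradictory, and that model details often sit in an analysis plan that is not shown. This stands as far as priority goes. It does not remove the scheduling gap or the choice of test, both of which the article states.

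Four stronger readings are tempting, but the document does not support them.

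- **A sharp gain in power.** One baseline and one follow-up value at ρ = 0.7 give V = 1 − 0.49 = 0.51 and about 36 % power; four follow-up values give V = 0.775 − 0.49 = 0.285 and 57 %. That is the wrong comparator. The planned T0 + T1 and T2 + T4 already give V = 0.274 and 58 % under the same assumptions.
- **Routine values are discarded, or a lasting effect cannot be seen.** The article does not exclude routine values. T2 and T4 give an early and a 7-year reading, so only the course between them is unseen. Nor is T2 said to fall immediately at the end of therapy; the article says only that it comes after it.
- **The data are certainly there and free.** Serial HbA1c in the records or register is an inference. The Intention to treat section promises HbA1c without saying where it comes from. Routine values may come from other laboratories than the one under Measurements, and visit frequency may depend on glycaemic control.
- **No between-arm HbA1c comparison is intended.** The aim of Study I is to compare the arms. The defect is that the named test does not do so, and the regression is described only for baseline characteristics.

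**Conclusion.** The point holds as a minor improvement, mainly for Study I. The article fixes HbA1c at four visits, with about 6 to 6.8 years unobserved after T2, and the test it names is a within-group one.

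The clearest benefits are a visible course after therapy and better first-year precision than T2 alone, which persists across the decay range examined. Over the whole follow-up the gain in precision against T2 + T4 may be up to a third of the standard error or nothing at all. These sizes rest on assumed correlations, visit times and a constant 0.35 SD effect. If the effect fades, averaging dilutes it. In Study II the addition mainly fills in the course after T3.

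**What to change.** 1. In the sections on assessments at T0 to T4 and on data collection between measuring points, add retrieval of routine HbA1c values, with date and laboratory, between T0 and T4 for every randomised patient, from the records and register already accessed and where available. State what bi-annual means.
2. In Statistical analysis, compare HbA1c between randomised arms with a repeated-measures model adjusted for T0 and T1, with time in the model. Report the difference averaged over the first year after therapy and over T2 to T4, alongside the effects at the planned visits.

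**Cost:** a wider query in existing sources and one longitudinal model, with no added study visit. **Downsides to state:** irregular dates, which time in the model addresses; visit frequency that may depend on control, which it does not; possible laboratory differences; and a time-averaged estimand that answers a different question from the effect at a single visit.
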